## Abstract

**Background:**

The Turkish population living in the Netherlands has a high prevalence of psychological complaints and has a high threshold for seeking professional help for these problems. Seeking help through the Internet can overcome these barriers. This project aims to evaluate the effectiveness of a guided self-help problem-solving intervention for depressed Turkish migrants that is culturally adapted and web-based.

**Methods:**

This study is a randomized controlled trial with two arms: an experimental condition group and a wait list control group. The experimental condition obtains direct access to the guided web-based self-help intervention, which is based on Problem Solving Treatment (PST) and takes 6 weeks to complete. Turkish adults with mild to moderate depressive symptoms will be recruited from the general population and the participants can choose between a Turkish and a Dutch version. The primary outcome measure is the reduction of depressive symptoms, the secondary outcome measures are somatic symptoms, anxiety, acculturation, quality of life and satisfaction. Participants are assessed at baseline, post-test (6 weeks), and 4 months after baseline. Analysis will be conducted on the intention-to-treat sample.

**Discussion:**

This study evaluates the effectiveness of a guided problem-solving intervention for Turkish adults living in the Netherlands that is culturally adapted and web-based.

**Trial Registration:**

Nederlands Trial Register: NTR2303

## Background

Historically, the Netherlands has played an important role in Europe as a host country for immigrants. The immigration of guest workers became an important trend after World War II and changed the Netherlands into a multi-ethnic and multicultural society. Nowadays, almost one-fifth (19.9%) of the Dutch population was born outside the Netherlands (first generation migrants) or has one or both parents born outside the Netherlands (second generation migrants) [1]. Slightly more than half of these migrants (55%) come from non-western countries. The Turkish population is one of the main ethnic groups in Dutch society and constitutes 2.3% of the total population. About half of this group was born in Turkey (first generation), while the other half has parents who were born in Turkey (second generation). Migration is a complex process, which can have a immense impact on a migrant's life and mental health. It can improve the quality of life of migrants in the economic sense, but it can also involve complexities in the adjustment process, such as unemployment, minority status and tensions between generations [2].

One-third of the Turkish population living in the Netherlands has psychological problems such as depression and anxiety, which is a higher prevalence than normally found in general population studies [2]. The 1-month prevalence of depressive and/or anxiety disorders is highest among the Turkish migrant group (18.7%) in comparison with other ethnic groups (6.6% among Dutch and 9.8% among Moroccan) [3].Turkish women in particular currently have a strongly increased risk for developing depression compared to Dutch natives, and young Turkish women are at a high risk of attempting suicide [4].Despite the high risk of serious psychological problems among the Turkish population, they benefit to a much lesser extent from advances in evidence-based depression prevention services than the general population. Their mental health care service uptake is low and they often have a high threshold for seeking professional help for their mental health problems [5,6].

An innovative way to overcome the barriers referred to above is the Internet, which has low threshold acceptability, a high level of anonymity and offers flexibility in time and place. There is now convincing evidence that web-based interventions effectively reduce depressive symptoms and prevent depression [7-12] and they have been shown to be not only clinically effective, but also cost effective [13]. Little is known, however, about the effectiveness of these interventions in ethnic minority groups, although expectations are that these groups may also benefit from the interventions. Self-help through the Internet has the main advantage of a high level of anonymity and might overcome important cultural barriers. Since almost 80% [14] of the Turkish population in the Netherlands has internet access, it could be an ideal way of reaching and offering help to Turkish people with depressive symptoms.

One successful example of an evidence-based intervention is *Alles Onder Controle *(AOC). This is a web-based guided treatment defined as a standardized psychological intervention, which can be worked through independently by the clients themselves in their own homes. The clients receive weekly feedback from a trained coach by e-mail. *AOC *has a self-examination framework [15] and is based on problem-solving therapy, the core element being that clients learn to regain control over their problems and lives in a structured way. This method has been proven to be effective in several studies [16,17] and the statistical and clinical effectiveness of *AOC *in reducing symptoms of depression and anxiety among native Dutch have been shown in several studies [11,18]. It is still unknown, however, whether this intervention is also effective among ethnic groups, especially among the Turkish population, which is currently a high risk group for developing depression. No previous attempts have been made to adjust and examine *AOC *for Turkish migrants, although the limited studies available on depression interventions in other countries show that ethnic minorities can be effectively recruited and treated with prevention interventions [19-22].

In the present study, we will work with *AOC-TR*, the culturally adapted version based on the needs of the Turkish population that is available in Dutch and in Turkish. This online guided self-help intervention is intended to reduce depression complaints and the effectiveness of *AOC-TR *will be examined in a randomized controlled trial with adult Turkish people living in the Netherlands.

## Methods

### Study design

This study is a randomized controlled trial with two arms: an experimental group and a wait list control group. The experimental group obtains direct access to the guided web-based self-help intervention; the wait list control group receives access to the intervention after 4 months. The study protocol, information brochure and informed consent have been approved by the Medical Ethics Committee of the VU University.

### Inclusion and exclusion criteria

Turkish adults living in the Netherlands are eligible if they meet the following criteria: 1) age 18 years or older; 2) depressive symptoms (measured by the Center for Epidemiologic Depression Scale, CES-D score ≥ 16); 3) Turkish background (participant was born in Turkey or at least one of his/her parents was born in Turkey); 4) has access to a PC and the Internet and an e-mail address. Participants will be excluded if they are suicidal (according to the MINI-International Neuropsychiatric Interview).

### Recruitment

Recruitment will take place among the Turkish population in the Netherlands by means of advertisements in Dutch and Turkish national newspapers, magazines, community sites, and banners on health related websites for migrants. These advertisements contain a link to the research website with information about the study. Respondents who are interested can apply by sending an e-mail to the researcher. The information brochure and informed consent will be e-mailed together with the link for the screening.

### Randomization

After screening, participants will be randomized into one of the two conditions: the experimental group and wait list control group. The allocation schedule will be generated by an independent researcher using a computerized system. Those in the experimental condition will receive a username and password to log in to *AOC-TR*. Participants who are in the wait list condition will receive the same schedule of assessments online as the people in the experimental condition and receive a username and password to log in to the treatment after four months.

### Sample size

The sample size will be based on the expected difference of d = 0.45 on the primary outcome between the experimental and control groups. This expected difference is based on previous studies [10,11]. Based on a power (1-beta) of 0.80 in a two-tailed test, an alpha of 0.05, we need to start with 100 participants at baseline in each condition to show an effect-size of 0.45. The total sample size at baseline therefore, is determined as being 200 participants with depressive complaints.

### Interventions

#### Problem-Solving Treatment

The Dutch version of Alles Onder Controle has been adapted by:

- cultural sensitivity in the languages and presentation in relation to psychological problems

- use of culture-specific cases and problems that are recognizable for the target group concerned

- culture-specific examples of persons with similar problems

The intervention was translated into Turkish by a Turkish psychologist after adaptation and the translation was checked by two native speakers. Each participant is allowed to choose his/her language of preference.

The intervention consists of 5 sessions and takes 5 weeks in total. During that period the respondents indicate what they think is important in their lives, they make a list of their "problems and worries" and they categorize their problems into three groups: unimportant (not related to what they think is important in their lives), important and solvable (these problems are solved by a systematic problem-solving approach consisting of 6 steps), or important but unsolvable (having lost someone through death or having a chronic general medical disease for example; in the case of problems like these, they make a plan for how to live with them). The 6-step problem-solving procedure is the core of the intervention and people are stimulated to use this procedure during the course for several of their 'important and solvable' problems. The idea is that by mastering this technique people will regain mastery of their problems and ultimately their lives. At the end, participants will receive a certificate for completing the intervention.

#### Support

The participants are supported by trained coaches, whose feedback on the homework assignments done by the participants is given in brief weekly e-mails. The total amount of time spent on each participant is about 1.5 hours. It takes about 15 or 20 minutes per week per respondent to write these e-mails, which will be done by a bi-lingual psychologist at the VU University. The researcher (BU) will verify whether the coach has followed the treatment protocol sufficiently by reading a selection of the emails and by supervision.

### Assessments

All assessments will take place in the preferred language, either Dutch or Turkish. The primary outcome measure is the reduction of depression symptoms as measured by the CES-D, the secondary outcome measures are symptoms of anxiety, somatic symptoms, acculturation, quality of life and satisfaction.

The CES-D, one item on the Beck Depression Inventory-II (BDI-II) and Section C of the Mini-International Neuropsychiatric Interview (M.I.N.I) will be administered as screening measures. Suicide ideations and risk will be measured in two steps. Suicide ideations and risk will be measured in two steps. First, the suicide item on the BDI-II will be presented [23,24]. This instrument is validated among Dutch (e.g. [25,26]] and Turkish populations [27,28]. If the response is confirming, then the suicide risk will be measured with the suicidality section of the MINI [29,30]. The suicide section of the MINI consists of six items and quantifies respondents in four groups: no suicide risk, low suicide risk, moderate suicide risk and high suicide risk. Dutch [31] and Turkish [32] translations of the MINI will be used.

Assessments will take place before randomization (T_0_), after completing the treatment (6-8 weeks, T_1_), and four months after baseline (T_2_). An overview of the procedures the participants will undergo in this study is given in Figure 1. See table 1 for an overview of all assessments at each point in time.

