### Statistical analysis

The study will be carried out in accordance with the CONSORT guidelines. All analyses will be based on the intention-to-treat sample and missing values will be imputed by means of regression analyses. A t-test will be used to compare the post-test mean scores (at T_1 _and T_0_) for the intervention group with the post-test mean scores for the control group. For comparison of the two means Cohen's *d *will be used as the between effect size. Cohen's *d *will be calculated as the difference between the post-test mean scores of the intervention and the control group divided by the pooled standard deviation. Effect sizes of 0.8 are assumed to be large; effect sizes of 0.5 are moderate; and effect sizes of 0.2 are assumed to be small [51].

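### The primary t-test is set at an impossible post-test time (T0), and no passage fixes whether CES-D at T1 or at T2 is the primary comparison

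*Protocol article*

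**What the plan says.** - **Primary outcome (Assessments).** "The primary outcome measure is the reduction of depression symptoms as measured by the CES-D". No assessment time is given.
- **Schedule (Assessments, Table 1).** T0 is before randomisation. The later assessments are described as "after completing the treatment (6-8 weeks, T_1_), and four months after baseline (T_2"). CES-D is collected at all three. The wait list group gets access only after four months (Study design, Randomization), so T1 and T2 are both intended as comparisons of treated with not-yet-treated participants.
- **Abstract (Methods).** "Participants are assessed at baseline, post-test (6 weeks), and 4 months after baseline". Here the label post-test belongs to the 6-week assessment.
- **Sample size.** The calculation rests on an "expected difference of d = 0.45 on the primary outcome between the experimental and control groups". It continues: "Based on a power (1-beta) of 0.80 in a two-tailed test, an alpha of 0.05". One difference, one alpha, no time and no split.
- **Statistical analysis.** "A t-test will be used to compare the post-test mean scores (at T_1 _and T_0_) for the intervention group", set against the same means in the control group. Cohen's d is then defined on post-test means. T2 does not appear in this section.

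**The concern.** The sentence that should fix the primary comparison names a time at which it cannot be made. T0 is measured before allocation, so a difference between the arms there reflects chance and says nothing about the intervention. With T0 struck out, the reader must guess whether one time or two was meant, and the other sections do not settle it.

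Two things are at stake. First, a result that is significant at T1 but not at T2, or the reverse, has no prespecified reading, although CES-D is collected at both times before the control group gets access. Second, if the time were chosen once results were known, or if either time were allowed to count, the 5% error rate in the sample size section would no longer describe the trial's main claim.

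**Working it through.** **1. The plan's own figure.** Inputs from the Sample size section: d = 0.45, power 0.80, two-sided alpha 0.05.

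- Normal approximation: n per arm = 2(1.960 + 0.842)² / 0.45² = 15.70 / 0.2025 = 77.5, so 78. The exact two-sample t-test gives 79.
- The stated figure is 100 per arm. It matches one test at 0.05 if about 21-22% are lost: 79/(1 − 0.21) = 100 and 78/(1 − 0.22) = 100. No loss rate is stated, though the figure is given as the number to start with at baseline.
- With all 100 per arm evaluable, one test at 0.05 has power of about 0.89.

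The calculation is therefore for a single comparison, and nothing in it identifies T1 or T2.

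**2. The possible repairs of the T0 entry.**

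- *T0 refers to baseline*, either as the start of a T0-to-T1 change (in keeping with an outcome defined as a reduction) or as a baseline comparison. One post-randomisation test of CES-D remains, at T1.
- *T0 is a slip for T2.* Two post-randomisation tests of CES-D remain, with no order between them.

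The text does not exclude either.

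**3. Error rate under each repair.**

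- T1 only: 0.05, no inflation.
- T1 and T2, each at 0.05, with success claimed at either: error = 1 − P(|Z1| ≤ 1.96 and |Z2| ≤ 1.96), where Z1 and Z2 are bivariate normal with correlation ρ. At ρ = 0 this is 1 − 0.95² = 0.0975. The documents give no correlation, so a range is assumed:

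| ρ (assumed) | Family-wise error |
|---|---|
| 0 | 0.0975 |
| 0.3 | 0.095 |
| 0.5 | 0.091 |
| 0.7 | 0.083 |
| 0.8 | 0.078 |
| 0.9 | 0.070 |

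Independence is an upper reference rather than a likely value, since the same 20 items are answered by the same people about two and a half months apart or less.

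**4. What the remedies would cost.**

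- One named primary time: 78-79 evaluable per arm, as in step 1.
- T2 tested only after a significant T1, each at 0.05: if there is no effect at T1, a false claim requires a false positive at T1 (at most 0.05). If there is an effect at T1 but none at T2, the only false claim is at T2 (at most 0.05). The overall error stays at 5% and the T1 calculation is unchanged.
- For contrast, 0.025 at each time: 2(2.241 + 0.842)² / 0.2025 = 93.9, so 94 evaluable per arm (96 by t-test). With 79 evaluable per arm, power per test falls to about 0.72 (0.71 by t-test).

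**The case against.** The strongest reply is that T1 is plainly meant. The abstract gives the label post-test to the 6-week assessment and lists the 4-month one separately. The analysis section uses the same label for both the t-test and Cohen's d, and the planning value of 0.45 is that same kind of between-group effect size. Much of this stands, and it is why T1 is the natural time to name. It is still an inference: the analysis sentence attaches two times to post-test, one of them impossible, and no sentence makes T1 primary.

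A reader might infer more: that the plan makes two tests of the primary outcome at 5% each, so its error rate is already near 10%. The documents do not support that. T2 is absent from the analysis section, reading T0 as T2 is only one of the possible repairs, and nowhere is significance at either time said to be enough. A reader might also infer that the power claim belongs to neither time. That too is stronger than the text allows, because the wording leans towards T1.

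Finally, this is a journal article, and a testing order for follow-up times may sit in an analysis plan that is not shown. The absence of a multiplicity rule is therefore not the fault here. The fault is that the article does state the times of its main test and states them wrongly, while the time of the outcome on which the sample size rests is left implicit.

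**Conclusion.** The point holds in limited form. As written, the primary t-test names a pre-randomisation time as a post-test, and the primary time of CES-D is not fixed in any section. T1 is suggested but not designated.

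The effect on the error rate is conditional. It is nil if only T1 is tested. It is about 7-10% against a nominal 5% if T0 stands for T2 and either time may carry the claim; that range rests on two unadjusted tests at 0.05 and on assumed correlations from 0.9 down to 0. Whichever repair is right, discordant results at T1 and T2 have no defined reading until one time is named. The correction should be made because it determines what the trial may conclude.

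**What to change.** 1. In Statistical analysis, correct the parenthesis that lists T1 and T0.
2. State that the between-group comparison of CES-D at T1 is the sole primary test, at two-sided 0.05, and say in Sample size that d = 0.45 refers to that comparison.
3. Make CES-D at T2 secondary, tested for a confirmatory claim only if T1 is significant. Otherwise report the T2 estimate and its confidence interval descriptively.

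The other scales are already designated secondary and need no relabelling. The cost is one or two sentences, with no split of alpha and no additional participants. The choice should be recorded before outcome data are examined by arm.

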**Figure 1 F1:**
[figure not shown]
**Research procedure in flow diagram**.

**Table 1 T1:** Overview of instruments per measurement.

	Number of items	**T**_**0**_ (baseline)	**T**_**1**_ (6-8 weeks)	**T**_**2**_ (4 months)
1. Socio-demographic data	10	***x***		

2. Depressive symptoms (CES-D)	20	***x***	***x***	***x***

3. Anxiety (scale of HADS)	7	***x***	***x***	***x***

4. Somatic symptoms (scale of SCL-90)	12	***x***	***x***	***x***

5. Acculturation (LAS)	28	***x***	***x***	***x***

6. Quality of life (EuroQol 5D)	5	***x***	***x***	***x***

7. Satisfaction and track and trace	5		***x***	***x***

### Instruments

#### Depressive symptoms

Depressive symptoms will be measured using the Center for Epidemiologic Depression Scale (CES-D) [33]. It includes 20 self-rated items, each scored 0-3, and measures the severity of depression. The total score ranges from 0 (no feelings of depression) to 60 (severe symptoms of depression. The CES-D is available in Dutch and Turkish and both have been proven to have good psychometric properties in terms of validity and reliability [34,35]. The CES-D is also reliable and valid when presented digitally [36]. The optimal cut-off score varies in literature, but a score of 16 is usually regarded as indicating clinically relevant depressive symptoms [37].

#### Anxiety

The Anxiety scale of the Hospital Anxiety and Depression Scale (HADS) will be used to measure symptoms of anxiety [38]. The HADS consists of a depression scale and an anxiety scale with a total of 14 items. Each item can be scored with a 4-point Likert scale on a range of 0-3, where 0 refers to no anxiety and 3 to high anxiety. The total score range is 0-21. A score between 0 and 7 indicates no anxiety; a score between 8 and10 indicates possible anxiety; scores above 11 or12 are indicative of a clinical anxiety disorder. The HADS has been proven to be a valid and reliable instrument in various normal and clinical Dutch samples [39,40] and in Turkish samples [41].

#### Somatic symptoms

The Somatization (SOM) subscale on the Symptom Checklist-90-Revised (SCL-90-R) will be used for measuring somatic symptoms [42]. This is a five-point rating scale containing 12 items. Dutch and Turkish translations will be used for this study [43,44].

#### Acculturation

The Lowlands Acculturation Scale (LAS) will be used to measure the degree of acculturation [45,46]. It consists of 25 items that are rated on 6-point Likert-type scales with the extremes labelled as 'totally disagree' and 'totally agree'. The LAS can be divided into 5 subscales: Skills, Traditions, Social Integration, Values and Norms, and Feelings of Loss. The official Dutch and Turkish translations will be used, both of which have been validated [45].

#### Quality of life

The quality of life will be measured by the EuroQol Questionnaire (EQ5D) [47] in the official Dutch and Turkish translations, both of which have been validated [48-50]. This instrument consists of 5 items (mobility, self-care, usual activities, pain/discomfort, and anxiety/depression), each of which is rated as causing "no problems", "some problems", or "extreme problems". The score per item ranges from 0 (poor health) to 1 (perfect health).

#### Satisfaction and Track and Trace

A track and trace system will keep a record of the dates the participant logs on or finishes a lesson, and the number of e-mails sent to and received by the coach. This system will also ask the question "Was this lesson useful to you?" in Dutch and Turkish after each lesson and the answer can be given on a 5-point Likert scale.

